## Data analysis and management

### Sample size

The sample size for a three-arm cluster randomized trial was calculated using the WebPower software and selecting the omnibus test option considering an average of 50 children by school (cluster), a statistical power of 0.8, a significance level of 0.05, and an effect size of 0.5 on cognitive performance (selective attention using Das and Naglieri-Cognitive Assesment System) on the basis of a previous pilot study, according to the methods for this type of study proposed by Donner and Klark [36]. Taking into account these assumptions, the estimated sample size was 9 schools (clusters), three per arm. It should be noted that the number of subjects per cluster considers that the average number of students/classroom is 25, and schools with at least two classrooms were considered.

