**Methods:**

A three-arm cluster-randomized controlled trial (RCT) was carried out including eight schools (rural and urban areas) from Cuenca province, Spain. The schools were allocated to one of three groups: MOVI-da10-Enriched! intervention (*n* = 3), MOVI-da10-Standard! intervention, (*n* = 2), and the control group (n = 3). Around 900 children aged 4 to 6 years old were assesed at baseline (September 2017) and at the end (June 2018) of the intervention. The primary outcomes were changes in body fat by bioimpedance, executive function and motor competence. During a school year (from October 2017 to May 2018), children belonging to the MOVI-da10-Enriched! group performed enriched PA integrated into the academic curriculum including two active breaks lasting 10 min, 5 days/week. The children belonging to the MOVI-da10-Standard! group performed PA breaks (with low cognitive demand, where curricular contents were not reinforced) including two active breaks lasting 10 min, 5 days/week. In the control group, regular PA continued.

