### Cognition

Two core executive functions were measurement using two validated tests of the NIH toolbox battery [28] for the population aged between 3 and 85 years old. The Flanker Inhibitory Control and Attention test was used to measure inhibition/attention, this version includes a practice block of 4 trials, that children passed if they completed at least 3 trials. If so, a 20-trials block was presented consisting of a pseudorandom sequence of congruent and incongruent trials. Reaction time and accuracy percentage on incongruent and congruent trials were used as outcome of inhibition/attention; moreover, raw scores were attained [29]. Cognitive flexibility was assessed by the Stort dimensional change card test. Through this tool, schoolchildren should classify a series of bivalent test cards according to different dimensions of “color” or “shape”. First, a block of 4 trials was performed, from which participants had to pass three to get to the mixed 30-trial block randomly. Reaction time and accuracy percentage on pre-switch and post-switch trials were used as outcome of cognitive flexibility; in addition, raw scores were obtained [29].

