#### Physical activity

Was measured in a subsample of 500 randomly selected schoolchildren belonging to the IGs and the CG. PA was measured using GENEActive accelerometers (ActivInsights) for 7 consecutive days (including nights), with a fixed frequency of 30.0 Hz to record the data raw of acceleration measured in “g” for each movement axis (x, y and, z). The data were expressed in units of milli-g (1000 mg = 1 g = 9.81 m / s2) [32]. A valid measurement was considered for reports of at least 5 days, including one weekend day.

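### The stated 80% power is for nine schools, an omnibus test and a cognitive measure the trial does not use; it does not apply to the pairwise contrasts on eight schools at 3/2/3, and their power is not stated

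*Protocol article*

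**What the plan says.** The only power statement is in the Protocol article, Sample size. It was obtained by "selecting the omnibus test option considering an average of 50 children by school (cluster), a statistical power of 0.8". Alpha was set at 0.05, and the assumed effect was 0.5 for selective attention from the Cognitive Assessment System, taken from a pilot. The result was that "the estimated sample size was 9 schools (clusters), three per arm". No ICC is listed, and the text does not say whether 0.5 is a standardised mean difference (d) or Cohen's f.

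Other sections describe the trial differently:

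- **Schools.** The Abstract says: "A three-arm cluster-randomized controlled trial (RCT) was carried out including eight schools (rural and urban areas) from Cuenca province, Spain". Study design explains that nine schools were invited, one refused, and the remaining eight were then randomised: three to Enriched, two to Standard, three to control.
- **Tests.** Statistical analysis plans Model 1 (Enriched v control), Model 2 (Standard v control) and, only if both show significant cognitive improvement, Model 3 (Enriched v Standard). The propensity-score step also compares each intervention separately with control. No omnibus test is described.
- **Endpoint.** Under Cognition: "Two core executive functions were measurement using two validated tests of the NIH toolbox battery". The Cognitive Assessment System is not among the outcome measures.
- **Children.** The Abstract reports about 900 children at baseline, against 9 x 50 = 450 in the calculation.

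**The concern.** The published power claim and the published design do not match on number and allocation of schools, test, endpoint or cluster size. The article appeared in April 2019, after the final measurements of June 2018, yet the calculation was not restated for the eight schools randomised.

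Two things are at stake. A reader who sees 80% power may take a non-significant Standard v control result as evidence of no effect, although that contrast rests on two schools against three. In addition, Model 3 is fitted only if both control contrasts are significant, so the two-school contrast also decides whether Enriched and Standard are compared at all. The Background presents that comparison as an open question.

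**Working it through.** **Inputs from the article.** Sample size: 9 schools at 3/3/3, n = 50 per school, "a statistical power of 0.8, a significance level of 0.05", effect 0.5, omnibus test. Study design: 8 schools at 3/2/3. Abstract: about 900 children, so 900/8 = 112.5 per school.

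**Assumptions (not in the article).** The ICC, which is back-solved or shown as a range; the metric of 0.5, tried as d and as f; both interventions equally effective; total SD 1 with no gain from baseline adjustment; equal school sizes; tests on school-level degrees of freedom.

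**Formulas.** Variance of a school mean: V = ICC + (1 - ICC)/n. Let D be the difference of each intervention from control.

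- Omnibus: noncentral F on 2 and J - 3 df, with lambda = sum of k_j(mu_j - mean)^2 / V. For means (D, D, 0) this is 2D^2/V at 3/3/3 and 1.875D^2/V at 3/2/3.
- Pairwise: noncentral t, noncentrality D / sqrt[(1/k1 + 1/k2)V], with 4 df (3 v 3) or 3 df (2 v 3), two-sided 0.05.
- If 0.5 is f, then f^2 = 2D^2/9, so D = 3 x 0.5/sqrt(2) = 1.06 SD.

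**Step 1: the plan's own figure.** With F(2,6), 80% power needs lambda = 16.6.

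- d = 0.5, ICC 0.01, n = 50: V = 0.01 + 0.99/50 = 0.0298; lambda = 0.5/0.0298 = 16.8; power 80.5%.
- f = 0.5, ICC 0.118, n = 50: V = 0.118 + 0.882/50 = 0.1356; lambda = 2.25/0.1356 = 16.6; power 80%.

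Nine schools can thus be matched under either metric, but only by choosing the ICC. The figure can be neither confirmed nor refuted. With f = 0.5, nine is the smallest total reaching 80% for ICC about 0.089-0.118, or about 0.029-0.118 if the total was rounded up to equal arms.

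**Step 2: the design as randomised.** Example for d = 0.5, ICC 0.01, n = 50:

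- Enriched v control: 0.5/sqrt(0.0298 x 2/3) = 3.55 on 4 df, power 75.5%.
- Standard v control: 0.5/sqrt(0.0298 x 5/6) = 3.17 on 3 df, power 57.5%.

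| Metric | ICC | n per school | Omnibus 3/3/3 | Omnibus 3/2/3 | Enriched v control | Standard v control |
|---|---|---|---|---|---|---|
| d = 0.5 | 0.01 | 50 | 80.5% | 73% | 75.5% | 57.5% |
| d = 0.5 | 0.01 | 112.5 | 94.5% | 90% | 91% | 75% |
| d = 0.5 | 0.05 | 50 | 45% | 39% | 43% | 31% |
| d = 0.5 | 0.05 | 112.5 | 51% | 45% | 49% | 35% |
| f = 0.5 | 0.05 | 50 | 98% | 95% | 95% | 83% |
| f = 0.5 | 0.089 | 50 | 88% | 82% | 84% | 66% |
| f = 0.5 | 0.089 | 112.5 | 91% | 86% | 87% | 70% |
| f = 0.5 | 0.118 | 50 | 80% | 72% | 75% | 57% |
| f = 0.5 | 0.118 | 112.5 | 83% | 76% | 78% | 60% |

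The two rows with d = 0.5 and ICC 0.05 show sensitivity only. On that reading the planned 9 x 50 would itself have had 45%, so 0.05 cannot have been the planning value.

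**Step 3: a result that needs no ICC.** In units of sqrt(V), the difference detectable with 80% power is 3.07 for 3 v 3 schools and 3.89 for 2 v 3. The ratio is 3.89/3.07 = 1.27, so Standard v control needs a true difference about 27% larger, at any ICC and common school size.

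**The case against.** The strongest reply is that none of this proves a shortfall. The ICC and metric are unknown, and nine schools may have come from rounding up to equal arms. With f = 0.5 and ICC 0.05, both control contrasts exceed 80% even with eight schools of 50. The roughly 900 children also work in the trial's favour: at d = 0.5 and ICC 0.01 they lift Enriched v control to 91%. Adjustment for baseline, age and sex would help further. If, as an assumption, it removed 25% of the variance of school means, Standard v control in that same case would rise from 75% to 85%; at 50% it would reach 95%. The refusal of one school is disclosed, and sizing on a pilot's attention measure is ordinary practice.

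Much of this stands, and it rules out several stronger readings:

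- A reader might infer that the trial lacks 80% power for either control contrast, or that Standard v control is certainly under-powered. The documents do not give the figures needed to show that.
- A reader might infer that nine was miscalculated. It cannot be checked.
- A reader might see a contradiction in the accelerometer subsample of 500 exceeding the 450 planned children. A subsample of 500 from about 900 is coherent, and having more children than planned does not weaken power.

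The reply does not rescue the 80% statement itself. Disclosing eight schools is not the same as restating power for them, and no reading makes an omnibus calculation at 3/3/3 the power of a 2 v 3 contrast on a different test.

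**Conclusion.** The 80% figure does not apply to the schools, tests or endpoint of this trial, and the power of the planned contrasts is unstated and not recoverable from the article. This is a claim left standing for a different design, not an arithmetic error.

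Where the assumptions make 9 x 50 give about 80% omnibus power, the 3/2/3 design gives 75-91% for Enriched v control and 57-75% for Standard v control. If 0.5 is Cohen's f and the ICC is 0.05 or less, both exceed 80%. These figures assume equally effective interventions and no gain from baseline adjustment. That Standard v control is the weaker control contrast, for the same true effect and a common school size, does not depend on the ICC.

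**What to change.** Rewrite the Sample size paragraph for the trial as randomised, without adding schools:

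- eight schools at 3/2/3 with the actual children per school;
- the ICC used and the metric of the 0.5 effect;
- the NIH Toolbox score as the cognitive endpoint, with the reason if the pilot effect on the other test is carried over;
- power or minimum detectable difference for each pairwise contrast, with small-sample degrees of freedom and any assumed gain from baseline adjustment stated.

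Withdraw the 80% claim for any contrast that does not reach it. If the restated power of Standard v control is below 80%, say that a null result there is inconclusive, and that the absence of Model 3 for that reason is not evidence that the two programmes are alike.

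The cost is one paragraph. The downside is that the stated power may become less favourable.

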### Statistical analysis

The data of participants will be entered into a database by two independent researchers at the end of the measurements. Blinding on the handling of data will be assured by separating measurement values from the participant’s personal identification information. The statistical analysis will be performed in three steps. First, the effectiveness of the randomization processes will be evaluated through exploring the normal distribution of the variables and outliers using graphical procedures and the Kolmogorov Smirnov test. Social comparisons will be established between the CG and the two IGs, and subsequently, if appropriate, between MOVI-da10-Enriched! (IG-A) and MOVI-da10-Standardized! (IG-B).

Second, mixed regression models [37] will be used to evaluate the differences between the baseline and final variable measurements considering three models: Model 1 (1 = IG-A and 0 = CG), Model 2 (2 = IG-B and 0 = CG) and, if there is significant improvement in the cognitive performance of the IGs versus CG in the first two models, a third model (Model 3) will be made (1 = IG-A and 2 = IG-B). For these analyses, each outcome variable will be considered as independent, and the intervention as a fixed effect. Furthermore, the analyses will be adjusted for baseline data, age, sex and school (cluster). The results will be expressed in absolute differences in the changes in the variables between the baseline and the final measurements (95% confidence interval [95% CI]). When the dependent variable is prevalence of overweight/obesity, odds ratios and their 95% CI will be estimated.

## Discussion

Schools could be the ideal setting to help children meet PA guidelines. Physical Education classes and recesses have traditionnally been the periods of time in the school day in which students could accumulate PA, but nowadays, taking into account the decrease in the PA levels of students, and the rates of overweight and obesity, it seems necessary to explore new alternatives to increase PA time during the school day. Although numerous benefits related to both health and education of PA integrated in the classroom are promising, the results are not yet conclusive, and the results of the last reviews and meta-analyses highlight the need for more interventions in this area [15, 16, 39].

To our knowledge, MOVI-da10! is the first RCT addressing, in preschool children, the comparison of the effectiveness of two PA programs conducted in the classroom (enriched PA integrated into the academic curriculum and PA breaks only) on improving adiposity, executive function and motor competence. The secondary aim is to examine the impact of the programs on PA and improving health related quality of life or motor competence.

Some strengths of this study are that: i) it is conducted inside the school, which guarantees scaling up, since it is accessible to all students regardless of race, sex, ethnicity or family socioeconomic status. Additionally, no other institution has as much influence on children during the first years of their lives; furthermore, the mandatory nature of formal education could increase the effectiveness of this type of intervention [20]; ii) it has been shown that increasing opportunities for students to be physically active during the school day does not compromise academic performance [40]; iii) the program includes planned and structured activities, which are easily reproducible, but respects the teacher’s autonomy since they can decide what activity to do each day and at what time of the day, this fact could increase the acceptability of the program by teachers; iv) this study uses a standardized measure of cognitive function with established validity and reliability to be able to make comparisons with other studies; v) the use of an objective measure of PA that will allow knowing the exact intensity of PA breaks and the effect of MOVI-da10! in increasing the PA of children.

Some limitations should be mentioned. Although this is an RCT, children, parents and teachers could not be blinded regarding the allocation group and some bias could be derived from this fact. This bias was reduced by using a cluster randomization design. Additionally, during interventions, teachers may not implement PA breaks exactly as the researcher intended, thus adding some variability. Teachers might use PA breaks less frequently than planned, thus shortening duration or reducing intensity. This bias was minimized by training teachers, standardizing the program (providing pre-packaged PA breaks) and direct contact with teachers.

## Abbreviations

CG: Control group
CI: Confidence interval
IG: Intervention group
IG-A: MOVI-da10-Enriched! Intervention group
IG-B: MOVI-da10-Standardized! Intervention group
METs: Metabolic equivalents of task
PA: Physical activity
RCT: Cluster-randomized control trial
